## Analysis plan

Aim 1 (creation of a Trainer Manual) will not require formal data analysis. For Aim 2, all SBIRT trainers (n = 24–36) and all providers who receive SBIRT training (minimum n = 900) will be included in the statistical analyses [57, 58]. Prior to the main analyses, we will run descriptive statistics on the outcomes collected as part of Aim 2 to examine distributional properties, identify outliers, and transform variables as needed. Missing data will be imputed following recommendations of the National Research Council [59]. We will test the appropriateness of assumptions underlying the use of multiple imputation using sensitivity analyses [60].

For Aim 2 evaluation of trainer outcomes, the proportion of training sessions that met the fidelity benchmark will be examined as an outcome of interest, with the goal that at least 80% will meet the target. In addition, we will examine pre-training to post-training change in trainer SBIRT knowledge and proportion of trainers who attained the 70% knowledge benchmark immediately at the culmination of training.

For Aim 2 evaluation of provider- and patient encounter-level variables, change in each outcome will be examined over three distinct time intervals: 3-months pre-training to training (i.e., baseline reports of the past 90 days); training to 3-months post-training; and 3- to 6-months post-training. We will use longitudinal models to examine whether the provider- and patient encounter-level implementation outcomes significantly change across 3 assessments. Repeated measures and nested structures (due to providers being nested within trainers) will be accounted for by adding appropriate random effect terms. The longitudinal models will be estimated using generalized estimation equations which lead to robust standard error and statistical inferences [61]. Using the models, we will examine the outcomes of each post-training visit and compare them with the pre-training outcome. An omnibus test also will be conducted to compare all post-training visit outcomes with the pre-training outcomes. In addition to reporting statistical significance, we will report the effect size using Cohen’s d [62].

For Aim 3 exploratory analyses, we will test a series of multilevel models in which patient encounters (Level 1) are nested in providers (Level 2) which are nested within trainers (Level 3). Consistent with Raudenbush and Bryk’s multilevel modeling strategy, the proportion of variance to be explained at each level will be examined as an initial step [63]. Next, following a decomposed-first strategy that advocates for starting with moderation-focused hypotheses to avoid biases associated with conflated effects, we will conduct multilevel regressions testing the extent to which any putative covariates significantly moderate the hypothesized relationship among the variables [64]. We will test putative covariates (e.g., years of experience, biological sex, population group) at two levels: trainer and provider. All tests of moderation will adjust for the multi-level nature of the nested variables. If moderation is not found (e.g., if biological sex of the trainer does not moderate the effect of fidelity on provider attitudes), covariates will be controlled for as predictors. The goal of these analyses will be to determine the proportion of variance in patient encounter-level outcomes accounted for provider-level outcomes, and the proportion of variance in provider-level outcomes accounted for by trainer-level outcomes, after controlling for putative covariates. These data will help to elucidate mechanisms of action underlying the train-the-trainer cascading model.

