##### Post-training data capture

To evaluate the impact of training, attendees of the SBIRT training will commence recording data on their delivery of the AUDIT during patient encounters immediately after training with continuous recording of data for 6 months. As elaborated in the Measures section, patient encounter data will be tracked via programmed tablets or scannable paper forms, which will depict the AUDIT items and scoring algorithm.

Tablets and high-speed scanners will be offered to the partner organizations as an incentive for study participation: incentives are offered at the organization-level, reflecting the organization-wide focus of the train-the-trainer strategy. Each tablet and scanner will come with a brief user guide with step-by-step images showing how to answer the AUDIT questions using the technology. Tablets will enable off-line data collection and automated scoring using a highly intuitive user interface and robust data capture system, based around a platform called Survey2Go, though eventual connection with internet will be needed to submit data to the research team.

Our research team has developed and tested pre-programmed tablets as assessment administration and data collection tools with health professionals and lay workers in prior studies in South Africa [53]; the system has been applied in a wide range of contexts in South Africa ranging from no- to low-bandwidth, intermittent electricity, and in community and clinical contexts in both urban and rural areas. When tablets are not available or pragmatic such as in remote areas where even periodic internet connection is unlikely, providers will administer the AUDIT on user-friendly, one-page scannable forms using paper and pencil. Scannable forms will be sent to the research team in weekly batches for cleaning and aggregation.

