#### Patient encounter-level measures

To evaluate how SBIRT training impacts provider-patient encounters, we will measure data from all patient encounters in the participating units of organizations in real-time using brief session report forms. These forms will be collected via programmed tablets and/or scannable forms administered by providers to patients. Patient encounter-level data will include the patient’s gender, race, HIV status, and whether the patient is currently receiving HIV treatment.

Additional fields will include documentation of the AUDIT screening results. The first two fields will be used to indicate (1) whether or not the patient is screened for alcohol use (yes/no) and (2) scores for each of the 10 items on the AUDIT. When completed via tablet, the sum of AUDIT items contained in Question 2 will auto-calculate. When completed via paper, providers will be given a basic scoring template to calculate and interpret the score. A user-friendly table will be provided that summarizes the patient’s risk level and recommended intervention in accordance with the risk algorithm(modeled after Table 1), while the tablet will directly indicate which level of care is recommended. This will result in field (3) recommended action based on AUDIT (which will either be automated on the tablet or clearly noted on the paper forms based on score), and then the provider can enter field (4) final action taken (no action taken, positive feedback / encouragement about drinking given, brief intervention provided, or brief intervention provided with referral to specialty care). Data collected using these fields will be used to assess a patient encounter-level measure of reach, calculated as the proportion of total patient encounters over the specified recall time period during which the patient received screening, brief intervention, and referral to treatment.

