## Discussion

This protocol is designed to gather comprehensive data on multi-level factors associated with the implementation of SBIRT in HIV care settings throughout South Africa. Building upon the scaffolding and collaborative networks established by the South Africa International TTC, the proposed study will enable us to first codify and then evaluate an SBIRT train-the-trainer cascade model on implementation outcomes at multiple levels—trainer-level (i.e., knowledge, fidelity), provider-level (i.e., attitudes, confidence, acceptability), and patient encounter-level (i.e., reach of SBIRT to eligible patients).

It will be important in carrying out this protocol that operations are able to be readily adapted across a broad range of clinical and community care environments for individuals dually at risk for HIV and problem alcohol use, and as challenges arise. For example, this protocol will require work across a range of environments for training and intervention delivery, and there will likely be differences across organizations and units within organizations in familiarity with and access to technology. Further, as the COVID-19 pandemic continues to evolve, there will likely be need for more remote rather than in-person interactions as initially planned. Accordingly, the South Africa International TTC will develop the master training manual for both face-to-face and virtual delivery to ensure maximum flexibility. Any other adjustments made in response to the COVID-19 pandemic will be documented on an ongoing basis.

Findings from the research described in this protocol will be subject to important limitations. First, due to the lack of an integrated medical record system for consistent tracking both within and across our partner organizations, we will not be able to obtain true patient-level data. Instead, we rely on patient encounter-level data captured in real time using case report forms. The real-time nature of data collection will bolster confidence in data accuracy, but the data collected will only be as strong as the data entered, and may be subject to limitations as a result of both organization and provider adherence with the protocols. Second, while we are striving to work across a wide range of clinical and community care environments, and in a wide range of geographic locations, our data may not be generalizable beyond our partner organizations.

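### As written, pre-training encounter rates come from 90-day retrospective reports and post-training rates from real-time forms, so the pre-post contrast for these outcomes mixes training with a change of instrument

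*Protocol article*

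**What the plan says.** **Before training.** The Analysis plan defines the first interval for provider and encounter outcomes as "3-months pre-training to training (i.e., baseline reports of the past 90 days". It does not say who reports or with which tool.

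**After training.** Under Post-training data capture, attendees "will commence recording data on their delivery of the AUDIT during patient encounters immediately after training with continuous recording of data for 6 months", on tablets or paper forms "which will depict the AUDIT items and scoring algorithm". Under Patient encounter-level measures, "we will measure data from all patient encounters in the participating units of organizations in real-time using brief session report forms". Reach is derived from the fields of that form, yet the same sentence has it "calculated as the proportion of total patient encounters over the specified recall time period".

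**The test.** In the Analysis plan, "we will examine the outcomes of each post-training visit and compare them with the pre-training outcome", and an omnibus test will "compare all post-training visit outcomes with the pre-training outcomes". Power analysis and sample size treats screening, brief intervention and referral rates as the primary outcomes (Table 3).

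**Other sources.** The Discussion says that true patient-level data cannot be obtained "due to the lack of an integrated medical record system for consistent tracking both within and across our partner organizations". It credits real-time capture with supporting accuracy and does not mention the retrospective baseline among the limitations.

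**The concern.** Real-time forms cannot supply a pre-training value, because they begin after training. Read as written, the pre-training rate is a retrospective summary over 90 days and the post-training rate is a count from forms completed encounter by encounter. These two methods can give different rates for the same practice.

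The protocol describes no control arm, and every provider changes instrument at the moment of training. The instrument effect and the training effect therefore coincide, and neither the longitudinal model nor imputation can separate them. More providers narrow the interval around the sum of the two but do not remove the bias.

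The pilot gives no guide to the shift, because it used one self-report tool for both periods. At stake is the encounter-level part of Aim 2, which is also the part on which the sample size is built.

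**Working it through.** **Which instrument serves which period**

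| Period | Source as written | Section |
|---|---|---|
| 90 days before training | Retrospective baseline reports | Analysis plan |
| 0-3 months after | Real-time form fields | Post-training data capture; Patient encounter-level measures |
| 3-6 months after | Real-time form fields | Same |

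The contrast of the second and third rows uses one instrument. The contrasts of either with the first use two. The only text that points elsewhere is the recall wording in the definition of reach.

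**Reproducing Table 3**

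Inputs from Power analysis and sample size: referral 10% to 15%, correlation 0.3, two-sided alpha 0.05, power 0.80, stated n = 488.

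For one binary outcome per provider at two times,

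V = p1q1 + p2q2 − 2ρ√(p1q1·p2q2), and n = (1.960 + 0.842)² V / (p2 − p1)².

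V = 0.0900 + 0.1275 − 0.6 × √(0.0900 × 0.1275) = 0.2175 − 0.0643 = 0.1532.

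n = 7.849 × 0.1532 / 0.0025 ≈ 481, rounded up to 482, against 488 stated. The same formula comes within 3%, or within 2 providers, of all 18 rows. It is therefore a fair basis for showing size.

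**Pure instrument shift, no training effect**

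Let the recorded post-training rate exceed the reported baseline by an assumed shift d, with true practice unchanged. Then SE = √(V/n), z = d/SE, and the probability of a significant result is Φ(z − 1.96) + Φ(−z − 1.96). Expected attrition of 20% leaves 900 × 0.8 = 720 providers.

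Referral, p1 = 0.10, n = 720:
- d = 2 points: V = 0.1371, SE = 1.38 points, z = 1.45, probability 0.31
- d = 3 points: V = 0.1426, SE = 1.41 points, z = 2.13, probability 0.57
- d = 5 points: V = 0.1532, SE = 1.46 points, z = 3.43, probability 0.93

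Both outcomes at both sample sizes:

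| Shift | Referral, 720 | Referral, 900 | Screening (25%), 720 | Screening (25%), 900 |
|---|---|---|---|---|
| 2 points | 0.31 | 0.37 | 0.18 | 0.21 |
| 3 points | 0.57 | 0.66 | 0.34 | 0.41 |
| 5 points | 0.93 | 0.97 | 0.72 | 0.81 |

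Going from 720 to 900 raises every entry. With 900, the shift that is declared significant 80% of the time is about 3.6 points for referral and about 5 points for screening. For comparison, the pilot's referral rate moved by 3 points (15% to 18%).

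**Shift in the other direction**

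Take a true referral rise from 10% to 15% with 900 providers. If the baseline is over-reported by 2, 3 or 5 points, power falls from 0.97 to about 0.61, 0.31 or 0.05.

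**The case against.** The strongest reply is that the text does not settle the sources. The baseline reporter is not named. The definition of reach refers to a recall period, which fits real-time capture poorly. Phase 2 procedures lists data collection before training, after it, and at 3 and 6 months, and the Analysis plan speaks of post-training visits. Table 2, which holds the measurement schedule, is not reproduced in the text at hand, and this is a condensed article. Parallel recall after training may already be intended. This stands in part: a reader might infer that the protocol states provider recall at baseline and forms only afterwards, but the first is an inference. It is a strong one, because providers give data immediately before training, forms start later and there is no integrated record. If parallel recall is intended, the sections still conflict, because reach is said to be calculated from the form fields.

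A reader might also infer that the form is simply the AUDIT and so produces the behaviour it counts. The documents do not support that much. The form has a separate yes/no field for whether screening took place and allows an entry of no action, so it can record unscreened encounters. Because the AUDIT algorithm is central to the training, prompting by the form is arguably part of what is being implemented.

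On size, referral at 10% is the most sensitive case, and Aim 2's own list of encounter outcomes names only screening and brief intervention. Table 3 plans changes of 15 to 35 points for screening and 20 to 40 for brief intervention, against which 2 or 3 points is small. The calculation also ignores clustering by trainer, which would tend to widen the SE and lower these probabilities. All of this is fair. It limits the size but does not remove the confounding.

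**Conclusion.** The concern holds for the pre-post contrasts of screening, brief intervention and referral. As written, they compare a retrospective report with form counts, with no control arm and no planned bridging between the two, and the sections need to be reconciled on the source for each period.

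A reader might infer that the whole of Aim 2 fails. It does not. Trainer knowledge and fidelity do not use these data, the provider scales use the same questionnaires at all timepoints, and the 0-3 versus 3-6 month comparison stays within the forms.

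A reader might also infer that the effect of training will be overstated. The documents give neither the size nor the direction of the shift. The probabilities shown rest on assumed shifts, a correlation of 0.3, one binary outcome per provider and no clustering. Under those assumptions, a shift of a few points is enough to produce or hide a significant referral result, while screening is less sensitive.

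This is a choice about data collection, so analysis cannot repair it once training has begun. The Data Availability statement says that recruitment had not started, so the change could still be made in time.

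**What to change.** 1. State, consistently across Post-training data capture, Patient encounter-level measures and the Analysis plan, who supplies the encounter rates in each period, with which instrument and over which denominator.
2. Repeat the identical 90-day items at the 3- and 6-month provider assessments already scheduled. Base the pre-post test of the three encounter rates on that same-instrument contrast.
3. Use the real-time forms for the post-training level, the 0-3 versus 3-6 month trend and Aim 3.
4. Report forms against baseline only as a secondary result, with a sensitivity analysis over a stated range of instrument shifts in both directions.
5. Report the gap between recall and forms at 3 and 6 months as a check on agreement. It is tempting to read that gap as the baseline recall bias, but by then providers have been trained and have kept forms for months, which was not so at baseline.
6. Add the change of instrument to the limitations in the Discussion.

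The cost is a few extra items on two existing surveys and some rewording. The downside is that the main pre-post contrast then rests on self-report by trained, unblinded providers, who may over-report what they were taught. That should be stated with the result.

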#### Participants

Participants will include a total of 24–36 trainers and 900 providers embedded within three distinct organizations (8–12trainers and 300 providers per organization). We will partner with three organizations or departments responsible for provision of HIV services, each of which has broad reach in HIV endemic regions and has a productive relationship with the South Africa International TTC. To be eligible for this protocol, partners must provide healthcare services to individuals in key populations either diagnosed with HIV or at heightened risk of HIV-related consequences (e.g., sex workers, inmates in correctional facilities, adolescent girls and young women). Each partner organization will nominate staff to receive SBIRT instruction from the South Africa International TTC and to become certified SBIRT trainers. To be selected as an SBIRT trainer, individuals must meet the following criteria: (a) be currently registered with a regulatory body relevant to HIV care (e.g., registered counselor, nurse, medical doctor, psychologist, social worker); (b) have been with their current organization for at least 1 year; and (c) have experience providing training and/or supervision to direct front-line treatment providers. Following nomination by their organization, the South Africa International TTC team will conduct a brief screen to confirm eligibility.

At each organization, the 8–12 SBIRT trainers will in turn roll-out the curriculum to a minimum of 300 providers (average training size = 25–30 participants), thereby reaching approximately 900 providers in Years 2–4 (300 providers per organization * 3 organizations = 900 providers). Providers selected to receive the training will include the full range of treatment providers whom our partner organizations seek to train in effective alcohol screening and brief intervention. Based on our initial needs assessment, we expect our training attendees to be predominantly (approximately 70%) lay workers, with some representation of registered counselors, nurses, doctors, psychologists, and social workers. We also expect the demographics of the behavioral health workforce (both trainers and providers) to generally mirror the composition of the South African population, as reflected in the most recent census: Black African (80.2%), White (8.4%), Coloured—a South African census term for a multiracial ethnic group—(8.8%), Indian (2.5%), and Other/Unspecified (0.5%; [52]).

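### The Aim 2 models handle trainer clustering with random effects but are estimated by GEE, so the cluster level behind the claimed robust inference is not fixed

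*Protocol article*

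**What the plan says.** The Analysis plan describes the Aim 2 longitudinal models in two consecutive sentences, the first on the dependence structure and the second on estimation. Repeated measures and the nesting of providers within trainers "will be accounted for by adding appropriate random effect terms. The longitudinal models will be estimated using generalized estimation equations", and the second sentence adds of these equations: "which lead to robust standard error and statistical inferences". These models are to show whether provider- and encounter-level "implementation outcomes significantly change across 3 assessments". They supply the comparison of each post-training visit with pre-training and the omnibus test of all post-training visits.

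The three-level models described next in the same section (encounters in providers in trainers) are genuine multilevel models, but they serve only the exploratory Aim 3.

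**The concern.** A random-effects model and GEE treat clustering differently. The mixed model gives each trainer and provider a random deviation. GEE models the mean, uses a working correlation, and takes its variance from a sandwich over clusters assumed independent. As written, the device named for trainer clustering does not exist under the estimator named for the same model. The claim of robust inference then rests on which unit is the independent cluster, and that is not stated.

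The choice matters because every Aim 2 test of change in provider and encounter outcomes uses this model. A constant trainer effect cancels from within-provider change, but an effect of the trainer on the change does not. Such an effect is plausible here. The pre-training measurement precedes the trainer's teaching, so trainer quality can act only on later values. The Abstract also hypothesizes that trainers explain a sizeable share of provider-level variability.

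**Working it through.** **Inputs from the protocol.** The Analysis plan states "all SBIRT trainers (n = 24–36) and all providers who receive SBIRT training (minimum n = 900) will be included", so there are 900/36 = 25 to 900/24 = 37.5 providers per trainer. Expected attrition of 20% (Power analysis and sample size) leaves 900 × 0.80 = 720 completers, or 20 to 30 per trainer. Alpha is 0.05 two-sided. One pre-training and two post-training assessments make the omnibus test a 2-df test.

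**Assumed input.** The protocol gives no trainer ICC of change; 0.01 to 0.05 is used here.

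**The plan's own figure.** Table 3 gives 488 for referral rising from 10% to 15% with repeated-measure correlation 0.3. The paired-proportion formula, with providers independent, is

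n = (1.960 + 0.842)² × [p₁q₁ + p₂q₂ − 2ρ√(p₁q₁p₂q₂)] / d²
= 7.849 × [0.0900 + 0.1275 − 0.6 × √(0.0900 × 0.1275)] / 0.05² = 481.1, i.e. 482.

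A McNemar-type version gives 487. The paired formula puts the other 17 rows 1 to 6 below the printed values. Table 3 therefore contains no trainer term, so the provider-only reading cannot be dismissed as fanciful.

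**Reading 1: GEE clustered on provider.** With DEFF = 1 + (m − 1) × ICC, the actual error of a nominal 5% test is 2[1 − Φ(1.96/√DEFF)]. For example, with m = 37.5 and ICC = 0.05, DEFF = 1 + 36.5 × 0.05 = 2.825, 1.96/√2.825 = 1.166, and the error is 24.4%. The last column is a simulation with no true change (720 completers, unequal trainer sizes, 8,000 data sets per setting).

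| ICC of change | Trainers | DEFF (900) | Error, formula | Error, simulated (720) |
|---|---|---|---|---|
| 0.01 | 36 | 1.24 | 7.8% | 7.0% |
| 0.01 | 24 | 1.365 | 9.3% | 8.3% |
| 0.02 | 36 | 1.48 | 10.7% | 10.4% |
| 0.02 | 24 | 1.73 | 13.6% | 12.1% |
| 0.05 | 36 | 2.20 | 18.6% | 17.3% |
| 0.05 | 24 | 2.825 | 24.4% | 22.5% |

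A second simulation used a binary outcome at 25%, about 900 providers, three time points, unequal trainer sizes and 4,000 runs per setting. Its Monte Carlo standard error near 5% is √(0.05 × 0.95/4000) = 0.34 points. With a constant trainer effect but no trainer-by-time variance, provider-clustered error was 5.0-5.5% for a single contrast and 5.5-5.9% for the omnibus test. With trainer-by-time variance of 0.05 on the latent scale, it was 15.9% (36 trainers) and 20.8% (24) for a single contrast, and 21.4% and 28.7% for the omnibus test.

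**Reading 2: GEE clustered on trainer, uncorrected sandwich, z or chi-square reference.** The same binary simulation, over trainer-by-time variances from 0 to 0.10, gave:

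- 24 trainers: 6.8-7.5% for a single contrast, 9.0-9.9% for the omnibus test.
- 36 trainers: 6.1-7.3% for a single contrast, 7.7-8.7% for the omnibus test.
- With k trainers, a k/(k−1) variance factor and t on k−1 df, a single contrast gave 5.0-6.0%. A corrected omnibus test was not simulated.

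**The case against.** The strongest reply is that the plan names trainer nesting as something to be accounted for. Provider-only clustering runs against that intent, and the largest error rates belong to that reading. This stands: those figures show what is at stake if the sentence on estimation is taken alone, not what the authors intended.

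Second, under trainer clustering the excess is 1 to 2 points for single contrasts. It also presumes an uncorrected sandwich with normal-theory tests, which the protocol does not state. Small-sample corrections are commonly left to an analysis plan, so their absence is not itself an error. This also stands. It leaves the contradiction in place, because that lies in what the text does say.

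Third, a random-effects specification implies a marginal covariance that could serve as the GEE working covariance, and the authors may mean this loosely. It is possible, but such a model contains no random effect terms at estimation, and its sandwich variance still needs a named independent cluster.

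A reader might infer that the plan inflates type I error outright, even to around 30% (at an ICC of 0.10 the formula gives 28.8% with 36 trainers and 36.3% with 24). The documents do not support that. It needs both the provider-only cluster and a trainer-by-time ICC that they nowhere give.

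**Conclusion.** The contradiction is certain and sits in adjacent sentences: random effects are specified, and an estimator without them is named. Robust inference for Aim 2 cannot be claimed until the cluster level is fixed.

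The size is conditional. Under provider clustering, error is about 7-9% at an ICC of change of 0.01, about 17-24% at 0.05, and not materially raised at zero. Under trainer clustering, the reading closer to the stated intent, it is about 6-7% for single contrasts and about 8-10% for the omnibus test, if no small-sample correction is made. The ICCs, the uncorrected sandwich and the normal-theory reference are assumptions. Inflation is thus a risk that the wording leaves open, not an established property of the plan. It should be closed before the data are seen, so that the choice cannot depend on the results; the Data Availability statement says recruitment has not begun.

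**What to change.** Replace the two sentences with one of these:

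- **(a) Mixed model.** A generalized linear mixed model with trainer and provider random intercepts and trainer-by-time random effects, adding provider-by-time effects for encounter-level outcomes, where many encounters share a provider and period. Use small-sample degrees of freedom where available (for example Kenward-Roger for the scale scores).
- **(b) GEE.** The trainer as the independent cluster, a bias-corrected sandwich (Kauermann-Carroll or Mancl-DeRouen), and a t or F reference on about trainers − 1 df, that is 23 to 35.

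Either way, name the trainer as the top level and apply the same rule to the omnibus test. The cost is two sentences of text, standard software options and somewhat wider intervals. The design and sample do not change.
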